#### Intervention description {11a}

Patients randomized to the intervention group will have up to 4 visits daily from the dedicated MT to ambulate according to a standardized mobility protocol with a goal of 3 walks per day. The protocol will be initiated within 24 h of the baseline assessment. It will employ the Johns Hopkins Mobility Goal Calculator (JH-MGC, Fig. 1), [21] which prescribes a mobility goal based on the Johns Hopkins Highest Level of Mobility (JH-HLM) scale considering the most recent 6-Clicks score. The MT will complete the 6-Clicks assessment within each completed visit (i.e., one in which the patient gets out of bed). Nurses have demonstrated successful use of the JH-HLM and JH-MGC as guides for goal-setting and mobility achievement in this population [21, 26]. Per the protocol, patients with a 6-Clicks score of 16–17 will aim to achieve at least standing near the edge of the bed for ≥1 min with assistance from the MT. Patients with a score of 18–20 will have a goal of walking ≥10 steps with the MT. The MT will adjust each session’s goal consistent with the JH-MGC, accounting for the most recently recorded 6-Clicks score from the MT. The goals represent minimum targets—many patients will accomplish more. If a patient demonstrates appropriate tolerance and safety, MTs will encourage walking greater distances.

**Fig. 1 Fig1:**
[figure not shown]
The Johns Hopkins Mobility Goal Calculator to guide the standardized MT protocol (figure adapted from Klein et al. [21], with permission)

MTs will continue to visit patients even if their 6-Clicks score increases to >20. However, the intervention will be paused if the patient scores <16, since these patients will require more skilled care than could be safely provided by the MT. In this case, MTs will continue to visit the patient daily and resume the intervention when the 6-Clicks score (recorded by a nurse or physical therapist) is ≥16. The intervention will terminate after the completion of the 10th day from the baseline assessment or the day of hospital discharge, whichever comes first and regardless of how many days the patient received the intervention. Prior to discharge, the MT will provide those in the intervention group with a standardized written guide for continuing to walk at home.

Compliance with the intervention will be assessed immediately following each patient encounter by recording the following: (1) service time and duration (minutes); (2) 6-Clicks score; (3) target level of activity from the JH-HLM; (4) activity level achieved from the JH-HLM; (5) physical assistance provided for ambulation (Yes/No); (6) assistive device used for ambulation (none, walker, cane, IV pole, supplemental oxygen, other); (7) if service failed, reason why (patient unavailable, patient refused, MT ran out of time, other); and (8) any falls and whether an injury occurred.

#### Criteria for discontinuing or modifying allocated interventions {11b}

We will temporarily discontinue the intervention if a patient has a clinical deterioration of 6-Clicks score below 16, and resume it once they return to 16 or higher. Similarly, if a patient has an order for bed rest, we will temporarily discontinue the intervention until the bed rest order is removed.

Subjects may withdraw voluntarily from participation in the study at any time and for any reason. Participants will continue to be followed, with their permission, even if the study intervention is discontinued. In that case, all follow-up evaluations will take place on the normal schedule.

#### Strategies to improve adherence to interventions {11c}

To complete up to three walks daily, the MT will check with each patient up to four times each day. In addition, each MT will complete training in motivational interviewing, [40] a skill that will be used to encourage ambulation when patients may be resistant.

To ensure fidelity across sites, we will follow best practices as recommended by the NIH Behavior Change Consortium [41]. We will ensure that the treatment “dose” is consistent by standardizing the number of attempts and using the JHH-MGC tool to set target distances via the written protocol. MTs will record each contact and its outcome as described above, as well as any protocol deviations. To minimize “drift” in MT skills, [name] at CC and [name] at Baystate will conduct periodic observation. We will also arrange quarterly conference calls to share best practices, problem solve, and reinforce skills.

### Relevant concomitant care permitted or prohibited during the trial {11d}

No concomitant care will be prohibited during the trial. Patients may complete mobility activities with a nurse, family member, or, if consulted, an occupational or physical therapist.,

### Provisions for post-trial care {30}

There are no provisions for post-trial or ancillary care. There will not be any compensation for patients who may be injured during the trial.

### Outcomes {12}

The primary outcome will be change in mobility status at the conclusion of the intervention (hospital discharge or the 10th day of the intervention, whichever comes first) compared to the baseline assessment. Mobility status will be assessed at both time points using the Short Physical Performance Battery (SPPB), [42–44] a mobility performance assessment that can be administered in <10 min. It tests gait speed, repeated chair stands, and tandem balance, providing a gross assessment of functional balance, speed, and lower extremity power. It is safe and reliable for use with hospitalized older adults [45] and appropriately sensitive to mobility differences in that population [45, 46]. Further, the SPPB has demonstrated the ability to predict adverse health outcomes including in-hospital falls, [47] post-acute facility placement, [42] subsequent disability, [48] multi-morbidity, [42, 43, 49] and all-cause mortality [42, 50].

We will collect secondary outcomes at the time of hospital discharge including discharge disposition, length of stay, and the presence of hospital-acquired complications (falls, venous thromboembolism, pressure ulcers, and hospital-acquired pneumonia). Additional secondary outcomes will be assessed after hospital discharge and compared to baseline measurement of the same assessments: FRAIL scale score, [51, 52] the patient’s self-rated mobility status according to the AM-PAC mobility outpatient short form (compared to baseline AM-PAC 6-Clicks mobility scores using the AM-PAC T-scale), [53, 54] and the patient’s self-rated participation in activities of daily living using both the Index in Activities of Daily Living (Katz ADL) [55] and the Lawton Instrumental Activities of Daily Living Scale [56]. At this post-hospital time point, we will also assess 30-day hospital readmission and scores on the Patient Reported Outcomes Measurement Information System (PROMIS) physical function subscale [57, 58].

As both a secondary outcome and a method for characterizing the in-hospital mobility of both groups, we will use a medical grade accelerometer to measure steps taken, energy expenditure, activity bouts, sedentary bouts, body position, sleep latency, total sleep time, wake after sleep onset, and sleep efficiency. A random subset of 10–20% of patients discharged to home will continue to wear the device for an additional 10 days so that we can assess changes in activity immediately after discharge.

### Participant timeline {13}

The baseline assessment and randomization (T0) will occur for each patient within 48 h of hospital admission. They will be enrolled in the study until hospital discharge or after 10 days (T1), whichever occurs first. A post-discharge follow-up call from a study coordinator will be completed 30 days after enrollment (T2). This ensures that the time between T0 and T2 will be 30 days for every patient. The participant timeline, including assessments, is shown in Fig. 2.

**Fig. 2 Fig2:**
[figure not shown]
Participant timeline

### Sample size {14}

A sample size of 3000 has >99% power to detect a difference in SPPB change as small as 0.54 points (the MCID) between the two groups at a two-sided alpha of 0.05, assuming a common SD of 2.7 for the SPPB change, 20% non-compliance, 10% dropouts, and an interim analysis. The estimates for MCID and SD are based on observation of older acute care medical patients [43, 44]. Using these same assumptions, the power is still 92% for detecting a smaller difference of 0.35. Therefore, we expect ample statistical power for analyzing the primary outcome. The main reason for selecting this sample size is to ensure that the analyses of important secondary outcomes are not underpowered. The most important of these is discharge disposition, because even a small absolute difference in the number of patients discharged to home, as opposed to a skilled nursing facility, is clinically important. We will be able to detect a 7% difference in discharge to home vs. SNF with 98% power.

For other binary secondary outcomes (a combination of venous thromboembolism, pneumonia and falls, 30-day mortality, or 30-day readmission), the study will have 85% power to detect a 33% reduction assuming an 8% rate in the control group. Because these outcomes are not contingent on patient cooperation, we anticipate no dropouts. For secondary continuous outcomes such as length of stay, assuming 20% non-compliance rate, the power to detect a 4-h difference (0.167 days) is 95%.

Regarding the cost analysis, there is no accepted way of doing a power calculation. However, we tried adding $300 (an approximation of the cost of the intervention) to the costs of each of 1500 patients drawn randomly from a sample of 3000 Cleveland Clinic medical inpatients over the age of 65 with an AM-PAC 6-Clicks score between 16 and 20. We then performed a *t*-test on the log-transformed costs, as described in the economic analysis section, and we were able to detect the increase with a p-value of 0.03, indicating that should the intervention increase costs by an amount equal to the cost of the intervention, we should be able to identify it. Similarly, if the intervention decreases total costs by $300 or more (not including the costs of the intervention), we should have sufficient power to detect it.

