## Assignment of interventions: allocation

### Sequence generation {16a}

Randomization will be done using a computerized system. A block randomization scheme with a size of 4 will be used to ensure approximately equal numbers of patients per group. Allocation will be stratified within units within hospitals.

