Many potential limitations for our study are mitigated by the study’s design. For example, patients who are enrolled may be unable or unwilling to ambulate three times each day. If adherence is lower than expected in interim analyses, we will compare adherence rates across sites and attempt to identify and spread best practices. If that is not successful, we would still likely have sufficient power to detect a difference in our primary (>99% power with 70% adherence) and secondary outcomes (80% power with 70% adherence). Depending on the ease of enrollment, we may decide to enroll additional patients with the same resources. We anticipate heterogeneous patients, sites, and controls. Given our large sample, we anticipate that all of these important covariates will be balanced between the intervention and control arms. If we find that they are not, we will adjust our outcomes for important confounders. If we are unable to directly identify subgroups for whom the intervention is most beneficial, we will create a score, based on logistic regression, to identify patients who benefit if they score above a certain threshold. Alternatively, we will provide recommendations and tools to enable individual hospitals to incorporate our prediction model into the electronic health record and identify patients directly from the model.

While functional decline in the hospital is multifactorial, general out-of-bed mobility is a modifiable factor for many patients. This randomized controlled trial will test the effectiveness of MT-assisted ambulation on outcomes that matter to both patients and hospitals, including functional status, hospital discharge disposition, and the incidence of potentially avoidable hospital complications. It will also provide a useful estimation of cost implications to help hospital administrators assess the feasibility and utility of creating MT positions in their own hospitals.

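### The 92% power quoted for a 0.35-point SPPB difference allows for the 10% dropout but not for the 20% non-compliance it is said to include

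*Protocol article*

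**What the plan says.** The section Sample size {14} of the protocol article opens with the claim "A sample size of 3000 has >99% power to detect a difference in SPPB change as small as 0.54 points (the MCID"), tested "between the two groups at a two-sided alpha of 0.05", and gives the conditions as "assuming a common SD of 2.7 for the SPPB change, 20% non-compliance, 10% dropouts, and an interim analysis". The next claim but one is "Using these same assumptions, the power is still 92% for detecting a smaller difference of 0.35". The section then concludes that power for the primary outcome is ample.

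The section on statistical methods {20a} makes the main analysis intention-to-treat and compares SPPB change between the groups with an independent-samples t-test. Allocation is in equal numbers (Sequence generation {16a}).

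The Discussion returns to power where it considers patients who cannot or will not walk three times a day. There it says that the trial would probably still have "sufficient power to detect a difference in our primary (>99% power with 70% adherence"). It restates neither the target difference nor the dropout rate behind that figure.

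**The concern.** In an intention-to-treat comparison, non-compliers stay in their arm. If they benefit less, the expected group difference shrinks, and power falls with it. A calculation that truly contains 20% non-compliance should therefore give visibly less than one that contains dropout only, above all at a difference as small as 0.35, where power is not close to its ceiling.

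The 92% figure is the plan's evidence that the trial can also find effects below its own MCID. If non-compliance was left out, the chance of missing a true 0.35-point effect is understated, and readers are told that an allowance was made when it was not. The adherence figure in the Discussion raises the same question, because it is offered as reassurance should adherence fall.

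**Working it through.** **Inputs.** From Sample size {14}: 3000 patients, hence 1500 per arm at equal allocation; SD of SPPB change 2.7; two-sided alpha 0.05; 10% dropout; 20% non-compliance; differences of 0.54 and 0.35. From Interim analyses {21b}: one look at 40% with a boundary of 3.35. From the Discussion: 70% adherence.

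**Formula.** SE = SD × √(1/n₁ + 1/n₂), and power = Φ(δ/SE − 1.96), the opposite tail being negligible. If a fraction c complies and non-compliers keep a fraction r of the effect, the intention-to-treat difference is δ × [c + (1 − c) × r]. Controls are assumed not to receive the intervention.

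**Step 1: reproduce the plan's figure.** Dropout only: n = 1500 × 0.9 = 1350 per arm.

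- SE = 2.7 × √(2/1350) = 0.1039
- 0.35/0.1039 = 3.368, and Φ(3.368 − 1.96) = Φ(1.408) = **92.0%**

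This matches the printed 92% and leaves no room for non-compliance. A simulation with the interim look gives 91.9%, so the interim analysis does not matter here.

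**Step 2: add the 20% non-compliance as dilution, no benefit in non-compliers (r = 0).**

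- Difference = 0.35 × 0.8 = 0.28
- 0.28/0.1039 = 2.694, and Φ(0.734) = **76.9%** (76.6% with the interim look)

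**Step 3: vary the assumption about non-compliers** (20% non-compliance, 10% dropout). The documents do not give r, so the range is shown.

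| Share of effect kept (r) | Intention-to-treat difference | Power |
|---|---|---|
| 0 | 0.280 | 76.9% |
| 0.25 | 0.2975 | 81.7% |
| 0.5 | 0.315 | 85.8% |
| 0.75 | 0.3325 | 89.2% |
| 1 | 0.350 | 92.0% |

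**Step 4: count non-compliers as lost sample size instead.** This is not intention-to-treat, but it is another way the figure might have been built.

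- Removed from both arms: 1350 × 0.8 = 1080 per arm, power 85.4%
- Removed from the intervention arm only: 1350 against 1080, power 88.8%
- Intervention arm only with dropout ignored: 1500 against 1200, power 91.7%. This is close to 92% but leaves out the stated dropout.

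None of these variants reaches 92% with both stated losses included, unless non-compliers lose nothing.

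**Step 5: power at the MCID.** For 0.54 at 80% compliance with r = 0, the difference is 0.432; 0.432/0.1039 = 4.157 and Φ(2.197) = 98.6%. With r = 0.5 it is 99.7%.

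**Step 6: the Discussion figure.** The target difference (0.54) and the dropout rate (10%) are assumptions here.

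- r = 0: 0.54 × 0.7 = 0.378; 0.378/0.1039 = 3.637 and Φ(1.677) = **95.3%**. Without dropout (1500 per arm, SE 0.0986) it is 97.0%.
- r = 0.5: 0.54 × 0.85 = 0.459, power 99.3%.
- Non-adherers counted as lost patients: 1350 × 0.7 = 945 per arm, power 99.2%.

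**The case against.** The strongest defence is that 0.35 may mean the group difference as realised under intention to treat, after any dilution. The text does speak of a difference between the two groups. On that reading 92% is correct. What fails then is the claim that the same assumptions apply, since non-compliance plays no part in the figure. The section also uses a 20% non-compliance rate as a power input for length of stay, which suggests that it was meant to count. The sentence needs correction on either reading.

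A second objection stands in full: 77% and 95% both assume that non-compliers gain nothing, and the protocol does not say so. Its Discussion describes low adherence as falling short of three walks a day, so partial benefit is plausible. That makes the answer for 0.35 a range from about 77% up to just under 92%. It also means that the 70%-adherence figure can exceed 99% with half the effect retained, so the Discussion point is conditional.

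Three stronger readings are tempting and not supported:

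- A reader might infer that the claim of more than 99% at 0.54 is also wrong. The worst case is 98.6%, which is immaterial and passes 99% with modest partial benefit.
- A reader might infer that the plan treats low adherence as harmless. It does not: the Discussion proposes action across sites and quotes only 80% power for secondary outcomes at 70% adherence.
- A reader might infer that a null result would be misread. Such a result would be judged from its confidence interval, not from a planning figure.

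**Conclusion.** The power statement for 0.35 points is wrong as written. The figure of 92% contains the dropout and not the non-compliance. With both, and no benefit in non-compliers, power is about 77%, so the chance of missing a true 0.35-point effect is about 23% rather than 8%. On that same assumption, 92% power needs an effect of about 0.44 points in compliers (0.35/0.8). With half the effect retained, power is about 86%.

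The Discussion figure is a lesser and conditional matter: about 95% (97% without dropout) if it refers to 0.54 points with no benefit in non-adherers.

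A reader might go on to conclude that the trial is underpowered for its primary outcome. The documents do not support that. The 0.35 scenario lies below the stated MCID, power at the MCID is at least 98.6% at 80% compliance, and the plan says that the sample size was chosen mainly for the secondary outcomes.

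**What to change.** In Sample size {14}, choose one of two wordings:

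- Give the power for 0.35 points as about 77% with 20% non-compliance and 10% dropout, and state that non-compliers are assumed to gain no benefit. If partial benefit is thought realistic, state the share assumed and the power that follows.
- State that 92% applies to a realised intention-to-treat difference of 0.35 with 10% dropout, and remove non-compliance from the assumptions behind that figure.

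In the Discussion, state the difference, the dropout rate and the effect assumed in non-adherers behind the 70%-adherence figure, and correct it to match. Under 0.54 points, 10% dropout and no benefit it becomes about 95%.

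The cost is a text change. The first option makes the stated figure less favourable. The sample size, the analysis and the interim rule are unaffected.

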#### Secondary post-hospital outcomes

At 30 days post-discharge, a research assistant will contact participants to collect the additional secondary outcomes (FRAIL, Katz ADL, Lawton IADL, AM-PAC mobility, PROMIS physical function, and 30-day readmission). Contact will be initiated by subjects’ preferred means of communication, including telephone, email, patient portal, or text. Participants will be compensated for their time to respond. Based on preliminary efforts, we anticipate being able to contact 90% of the patients in 30 days. If we are unable to contact the patient, we will mail them the survey to complete on paper and return to our study team.

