Our study will be the largest randomized controlled trial to test any exercise intervention for inpatients and tests a simple intervention (walking up to three times per day with a MT) that would be feasible for most hospitals to implement. There will be adequate statistical power to not only detect important differences in the primary outcome of mobility status, but also in less common hospital complications (falls, venous thromboembolism, pressure ulcers, and hospital-acquired pneumonia) that have been suspected to be due, at least in part, to unnecessary bed rest. We will also be able to develop a clinically useful classification model, allowing hospitals to recognize for whom ambulation with a MT may be most beneficial. This classification model will be strengthened by specific data on mobility dosing that we will collect from accelerometers. Lastly, our data will provide clear estimates of intervention costs relative to potential cost savings, information that will be important to help hospitals decide if implementation of a similar program is feasible for them.

Our study has limitations. First, the analyses of dose effect are observational and subject to confounding, as is the heterogeneity of treatment effect analysis to determine which patients benefit most. The cost analyses will suffer from some missing data. We may also have missing data for our primary outcome if patients go home without our knowing. Also, it is not clear whether the AM-PAC mobility measures can be reliably assessed by patient versus clinician raters at different time points without introducing measurement error [26, 75, 76].

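### The 85% power for the binary secondary outcomes leaves out the section's own 20% non-compliance; with it, power is about 62–63% unless the 33% reduction is already a net intention-to-treat effect

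*Protocol article*

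**What the plan says.** The Sample size section opens with the primary outcome: "A sample size of 3000 has >99% power to detect a difference in SPPB change as small as 0.54 points (the MCID", under 20% non-compliance, 10% dropouts and an interim analysis. It then explains that N was set mainly for the secondary outcomes and gives three further power figures.

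- **Discharge disposition**, called the most important of them: "We will be able to detect a 7% difference in discharge to home vs. SNF with 98% power". No control rate is given and non-compliance is not mentioned.
- **Complication composite, 30-day mortality, 30-day readmission**: "the study will have 85% power to detect a 33% reduction assuming an 8% rate in the control group". The next sentence reads "Because these outcomes are not contingent on patient cooperation, we anticipate no dropouts". Non-compliance is not mentioned.
- **Length of stay**, with 20% non-compliance stated: "the power to detect a 4-h difference (0.167 days) is 95" per cent. No SD is given.

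The statistical methods section makes intention to treat the main analysis and uses a chi-square test for disposition and complications. The Discussion claims adequate power for the primary outcome "but also in less common hospital complications". It also says that with lower adherence the trial would probably still have enough power for its "secondary outcomes (80% power with 70% adherence"), without naming the outcome. On data source, Secondary post-hospital outcomes says that "a research assistant will contact participants to collect the additional secondary outcomes", lists 30-day readmission among them, and expects to reach 90% of patients.

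**The concern.** Dropout and non-compliance are different problems. Complete outcome data remove the first. They do nothing about the second: an intervention patient who does not walk stays in the intervention arm under intention to treat and pulls the difference towards zero. The section allows for this in words for the primary outcome and for length of stay, and the Discussion treats secondary power as dependent on adherence. The binary outcomes are left without the allowance.

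At stake is the stated reason for enrolling 3000 patients, and how a null result will be read. The Interim analyses section continues the trial past an efficacy crossing in order to assess the secondary outcomes. If power for complications is nearer 60% than 85%, a non-significant result says much less about absence of effect than the protocol leads readers to expect.

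**Working it through.** **Inputs.** From the Sample size section: 3000 patients, 8% control rate, 33% reduction, 20% non-compliance. From Sequence generation: equal allocation, so 1500 per arm. The two-sided alpha of 0.05 is stated for the primary outcome and assumed here for the secondary ones.

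**Formula.** Power = Φ[(|p₁ − p₂| − 1.96·SE₀)/SE₁], where SE₀ = √(2p̄(1 − p̄)/n) and SE₁ = √(p₁(1 − p₁)/n + p₂(1 − p₂)/n). With adherence c, and no benefit in non-compliers, p₂ = 0.08 × (1 − c × reduction).

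**Step 1: the plan's own 85%, full compliance.** For a one-third reduction p₂ = 5.33%, the difference is 2.667 points, SE₀ = 0.911 and SE₁ = 0.910 points. Then (2.667 − 1.96 × 0.911)/0.910 = 0.97, and power is 83.4%. Exactly 33% (p₂ = 5.36%) gives 82.6%; p₂ rounded to 5.3% gives 84.4%. So 85% is reproduced within rounding with no non-compliance.

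**Step 2: with dilution.**

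| Adherence | Net reduction (33% / one-third) | p₂ | Power |
|---|---|---|---|
| 100% | 33.0% / 33.3% | 5.36% / 5.33% | 82.6% / 83.4% |
| 80% | 26.4% / 26.7% | 5.89% / 5.87% | 62.4% / 63.3% |
| 70% | 23.1% / 23.3% | 6.15% / 6.13% | 50.5% / 51.4% |

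For 33% to be the net reduction at 80% adherence, the reduction in compliers would have to be 0.33/0.8 = 41%. For 80% power with dilution, a 40% reduction in compliers is needed: net 32%, p₂ = 5.44%, power 80.0%.

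**Step 3: disposition.** The control home rate is not given, so the rates below are assumptions. Effect: 7 points × adherence, 1500 per arm.

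| Assumed control home rate | 100% | 80% | 70% |
|---|---|---|---|
| 50% | 97.0% | 86.7% | 76.7% |
| 60% | 97.9% | 88.8% | 79.2% |
| 62% | 98.1% | 89.5% | 80.1% |
| 65% | 98.5% | 90.7% | 81.7% |
| 80% | 99.9% | 98.3% | 94.2% |

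A rate near 62% reproduces both published figures, 98% and 80%, if the 98% carries no dilution. A rate near 80% gives 98% with dilution, but then 94% at 70% adherence.

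**Step 4: length of stay.** The SD implied by 95% power is effect/[(1.960 + 1.645) × √(2/1500)]. With 20% non-compliance this is 0.8 × 0.167/(3.605 × 0.0365) = 1.01 days; without dilution it is 0.167/0.1316 = 1.27 days. If the SD were 2 days (an assumption), 0.1336/(2 × 0.0365) = 1.83 and power is Φ(1.83 − 1.96) = 45%. At an assumed 3 days it is Φ(1.22 − 1.96) = 23%.

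**Step 5: readmission.** If readmission is known only for the 90% reached, n = 1350 per arm, and diluted power falls further, to 58–59%.

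**The case against.** The best reply is that the section says only that a 33% reduction can be detected. A power statement may legitimately refer to the net between-arm difference, and then 85% is about right. Adherence is also graded, with up to three walks a day, so partial compliers may keep some benefit and 62% would be too pessimistic. Both points stand as conditions on the result. They do not rescue the text, which never says that the effect is net, although it mentions non-compliance for the outcomes on either side and lets secondary power fall with adherence in the Discussion.

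Other parts of the reply limit the point:

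- A reader might infer that 85% is not reached even at full compliance. That gap is rounding of the 33%.
- A reader might infer that the 98% for disposition is shown to be wrong. It is not: without a control rate, the omission of dilution there is only an inference from the 98% and 80% pair. Power also stays at about 87–91% at 80% adherence for assumed home rates of 50–65%, so the outcome named as most important is not seriously affected.
- The Discussion's 80% may have been meant for disposition. If so, 51% for complications does not contradict it, but the sentence is not limited to that outcome.
- No length-of-stay SD appears anywhere, so calling 1.0 day too small is a judgement. It rests on a design that excludes discharges planned within 24 hours and provides for stays beyond 10 days.
- For mortality, Retention after discharge already falls back on Medicare claims or the health record for vital status, and the expected 90% reach is before the mailed survey. The weakness in the zero-dropout premise is confined to readmission, for which no such fallback is stated.
- The primary outcome is safe: with 1350 per arm and 20% dilution, power for 0.54 points is about 98.6%.

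**Conclusion.** The concern holds in conditional form. The stated 85% is a full-compliance figure. Taking 33% as the effect in compliers, with no benefit in the rest, the section's own 20% non-compliance brings intention-to-treat power to about 62–63%, and to about 51% at 70% adherence. If 33% is the net effect, 85% is roughly right but implies about a 41% reduction in compliers, which is stated nowhere. Either way the text needs correcting.

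The length-of-stay figure is a separate weakness: it includes non-compliance but depends on an unstated SD of about 1.0 day.

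A reader might go further and conclude that the trial is too small, or that each single complication is hopelessly underpowered. The documents do not support the first, given the power for the primary outcome and probably for disposition. The second needs event rates that they do not give. At assumed control rates of 2% and 3%, power for a 33% reduction would be 29% and 41% even at full compliance. That is reason to qualify the Discussion's claim, but those rates are illustrative only.

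**What to change.** 1. In the Sample size section, apply the 20% non-compliance to the binary secondary outcomes and restate power as about 62–63%, or give the detectable effect (about a 40% reduction in compliers for 80% power). Alternatively, state that 33% is the net intention-to-treat reduction and give the complier effect it implies.
2. In the Discussion, name the outcome to which the 80% power at 70% adherence applies, and qualify the claim of adequate power for less common complications. Any single-complication power should show its assumed rate.
3. State the control home rate behind the 98% for disposition and whether that figure includes non-compliance.
4. State the length-of-stay SD and restate the power or the detectable difference. At 95% power with 20% non-compliance, the detectable effect in compliers is 3.605 × SD × 0.0365/0.8: about 0.33 days at an assumed SD of 2 days and 0.49 at 3.
5. Take 30-day readmission for all randomised patients from the health record and the Medicare claims already planned for the cost analysis, not only from the follow-up contact, so that the zero-dropout premise holds.

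The cost is revised wording and less favourable stated figures. Readmission would use data already being obtained. Neither the sample size nor the planned tests change.
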